### Data analysis

Statistical analysis will be realized on modified intention-to-treat (mITT) population, i.e. patients who received at least 1 injection of AGuIX nanoparticles.

The primary endpoint of phase I, the RP2D of AGuIX nanoparticles, will be determined as the highest dose tested for which the percentage of dose-limiting toxicities (DLT) is less than 33%. DLT percentage will be calculated for each tested dose. Progression-free survival, progression-free survival rate at 6 months and 12 months, and overall survival at 6 months and 12 months will be estimated by the Kaplan–Meier method in both arms. The primary endpoint of phase II, 6-month PFS in the experimental arm, will be calculated with its 90% CI, and the result will be interpreted according to the Fleming method.

Missing data will not be replaced. The statistical significance threshold is set at 5%. Statistical analyses will be performed using R software.

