## Methods / design

### Study design

NANO-GBM trial is a multicenter, phase I/II, randomized, open-label, non-comparative, therapeutic study.

The phase I part consists of a dose escalation with 3 dose levels of AGuIX: 50, 75 and 100 mg/kg, driven by a Time-to-event Continuous Reassessment Method (TITE-CRM) [16] with a dose-toxicity relationship given by a one-parameter power model and a priori risks of 5%, 10% and 25% for the 3 doses, respectively. The first patient will receive the first dose level, and the next cohorts will consist of 1 patient at a time, with a minimum of 6 treated at the recommended dose and a maximum of 12 patient treated in phase I.

The phase II part consists of a randomized open-label study. Patients will be randomized at baseline via a central system on eCRF, in a 2:1 ratio stratifying for the site and the age: one third of patients in the reference arm treated with radio-chemotherapy with concomitant TMZ (STUPP protocol), and two thirds in the experimental arm combining radio-chemotherapy with concomitant TMZ with the administration of AGuIX nanoparticles at the recommended dose determined in the phase I part. The randomization sequence is known only to the statistician. For the experimental arm, a single-stage Fleming design will be used. While the design does not allow for a formal comparison between the two arms, it may reinforce the value of the conclusions on the potential efficacy of the experimental treatment by validating the hypothesis on the control arm.

An interim analysis will be performed without interruption of inclusions for the independent data monitoring committee (IDMC) review, after 20 patients are treated in the experimental arm at the recommended dose (i.e. approximately 30 patients in phase II).

A maximum of sixty-six patients are expected to be enrolled: 12 patients in phase I, of which (minimum) 6 are treated at the recommended dose, 34 additional patients in the phase II experimental arm and 20 patients in the phase II reference arm. The study was started in March 2022 with a 2 years enrollment period and an estimated completion date by March 2026. This study has been registered on Clinicaltrials.gov (NCT04881032).

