#### Control group

Patients in the phase II reference arm will be treated with the standard STUPP protocol: RT at a dose of 60 Gy (30 fractions/6 weeks) and concomitant treatment with daily oral TMZ (75 mg/m^2^/day) from the first day of RT until the end of RT. Then, adjuvant TMZ will be reintroduced 4 weeks after the end of RT according to a 5-days schedule every 28 days (150 mg/m^2^/day for the first cycle and then at 200 mg/m^2^/day in the absence of toxicity).

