Week	**W19**	**W20**	**W21**	**W22**	**W23**	**W24**	**W25**	**W26**	**W27**	**W28**	**W29**	**W30**	**W31**	**W32**	**W33**	**W34**	**W35**		
Day	**126 ± 4d**	**133**	**140**	**147**	**154 ± 4d**	**161**	**168**	**175**	**182 ± 4d**	**189**	**196**	**203**	**210 ± 4d**	**217**	**224**	**231**			
Informed consent																			
Medical history and demographics																			
Initial histology / centralized review (FFPE tumor block)																			
Previous/concomitant treatments (including corticosteroids)																			
Evaluation of adverse events																			
Radiological evaluation MRI (disease)					✓												✓	✓	
MRI dosimetry																			
MRI post injection AGuIX (1 h after injection)^h^																			
Examination neurological (MMSE)					✓												✓	✓	
Clinical examination, weight	✓				✓				✓				✓				✓	✓	
Vital signs^a^	✓				✓				✓				✓				✓		
KPS Performance Index	✓				✓				✓				✓				✓	✓	
Serum pregnancy test^g^	✓				✓				✓										
Hematology^b^	✓				✓				✓				✓				✓		
Fasting biochemistry^c^	✓				✓				✓				✓				✓		
Urine analysis^d^	✓				✓				✓				✓				✓		
Pharmacokinetics^f^																			
Radiotherapy																			
Temozolomide	**5D**^**e**^				**5D**^**e**^				**5D**^**e**^				**5D**^**e**^						
AGuIX (injection IV)^i^																			
survival assessment																			✓

^a^vital signs include heart rate measurement, systolic and diastolic blood pressure, temperature, pulse

^b^hemoglobin, CBC platelet

^c^glucose, sodium, potassium, magnesium, calcium, total protein, creatinine, urea, AST, ALT, alkaline phosphatase, GGT, total bilirubin

^d^proteinuria

^e^TMZ 150—200 mg/m^2^/d D1 at D5 every 28 days (the daily dose of 150 mg/m^2^ for the first cycle will be increased to 200 mg/m^2^ for the 2nd cycle in the absence of significant toxicity)

^f^pharmacokinetics performed only for phase I patients: blood sampling 7 ml before injection, 15 min, 30 min, 1 h (before MRI), 2 h, 3 h, 4 h (before the beginning of radiotherapy), 6 h and 24 h post injection + urine collection during 6 h

^g^for patients of childbearing age

^h^only for patients receiving the experimental treatment: Phase I + Phase II experimental arm

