### Statistical analysis

#### Sample size

A maximum of 12 patients will be treated in phase I (sample size obtained by simulation, and in agreement with the bound obtained by Cheung’s formula, 2013), minimum 6 patients to be treated at the recommended dose, who will then be included and analyzed in phase II.

The phase II trial consists of a randomized study with a 2:1 ratio in favor of the experimental arm. For the experimental arm, a single-stage Fleming design will be used, based on an acceptable success rate of 70% and a 50% unacceptable success rate. In order to limit the one-sided alpha risk (of wrongly concluding that the treatment is effective) to 5% and the beta risk (of wrongly failing to conclude that the treatment is effective) to 20%, the minimum number of patients to include is 37. The treatment will be considered effective (and therefore the phase II positive) as soon as 24 successes out of 37 are obtained. In this case, the estimate of the probability of success will be of around 65%, with a 90% confidence interval (90% CI) of 51.4%-76.7% (Jeffreys interval).

It was decided to include 40 patients in the experimental arm, to compensate for a rate of about 10% of missing data (all reasons combined). Therefore, the number of patients in the reference arm will be 20.

Consequently, the total number of patients to be included is 66 (maximum): 12 patients in phase I, of which (minimum) 6 were treated at the recommended dose, 34 additional patients in the experimental arm of phase II, and 20 patients in the reference arm of phase II.

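### The only stated analysis population requires an AGuIX injection, so no reference-arm patient can enter it, although survival estimates are promised for both arms

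*Protocol article*

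**What the plan says.** The Data analysis section opens with the population: "Statistical analysis will be realized on modified intention-to-treat (mITT) population, i.e. patients who received at least 1 injection of AGuIX nanoparticles". The sentence covers the statistical analysis as a whole, with no limit by phase or arm. The article names no other population.

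Later in that section, progression-free survival, its 6- and 12-month rates, and overall survival at 6 and 12 months "will be estimated by the Kaplan–Meier method in both arms". The phase II primary endpoint, 6-month progression-free survival, is tied to the experimental arm and judged by the Fleming rule.

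The Control group section says: "Patients in the phase II reference arm will be treated with the standard STUPP protocol". It lists radiotherapy, concomitant temozolomide and adjuvant temozolomide, and no AGuIX. In the data collection schedule (Table 2), the AGuIX injections carry a footnote that reads "only for patients receiving the experimental treatment: Phase I + Phase II experimental arm".

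The Study design section rules out a formal test between arms but gives the reference arm a purpose: "it may reinforce the value of the conclusions on the potential efficacy of the experimental treatment by validating the hypothesis on the control arm". On its size, the Sample size section says: "Therefore, the number of patients in the reference arm will be 20".

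**The concern.** A population defined by exposure to the experimental drug cannot contain patients who are never offered it. Followed to the letter, the population sentence leaves the reference arm empty, and the promised two-arm estimates have nothing to be computed from.

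This is more than a missing detail that an analysis plan could be expected to supply. The article states a rule, and the rule conflicts with an analysis promised in the same section.

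The reference arm is the trial's only concurrent check on the 50% unacceptable rate. The Background section quotes 53.9% for 6-month progression-free survival under the standard regimen and says that prognosis is poorer in unresectable disease. The trial enrols only unoperated or partially resected patients. Whether 50% suits this population is therefore an open question, and the reference arm is there to inform it.

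If the contradiction stays, the analyst must choose a reference-arm rule (all randomised, started radiotherapy, or started temozolomide) in an open-label trial, possibly after outcomes are known.

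**Working it through.** **1. The plan's own design figures**

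Inputs from the Sample size section: unacceptable rate p0 = 0.50, acceptable rate p1 = 0.70, one-sided alpha 5%, beta 20%, and success declared with at least 24 of 37.

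- Fleming normal approximation: n = [(1.645 × √0.25 + 0.842 × √0.21) / 0.20]² = 36.5, rounded up to 37.
- Exact binomial: P(X ≥ 24 | n = 37, p = 0.50) = 0.0494, and P(X ≥ 24 | n = 37, p = 0.70) = 0.807. Both limits are met.
- Jeffreys 90% interval for 24/37, from Beta(24.5, 13.5): 51.4% to 76.6%. The article gives 76.7% for the upper limit, a rounding difference.

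The design reproduces. None of these figures depends on the reference arm.

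**2. Head count under the stated population**

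| Group | Planned | Can receive AGuIX | Can enter the stated population |
|---|---|---|---|
| Phase I | 12 (maximum) | yes | up to 12 |
| Phase II experimental, newly enrolled | 34 | yes | up to 34 |
| Phase II reference | 20 | no | 0 |
| Total | 66 | | up to 12 + 34 = 46 |

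The population sentence excludes 20 of 20 reference patients.

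**3. Which planned results survive the literal rule**

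- Phase I toxicity percentages by dose: unaffected, since phase I patients are given AGuIX.
- Fleming decision on 6-month progression-free survival: unaffected, since it uses the experimental arm only.
- Kaplan–Meier estimates in the reference arm: not computable, n = 0.
- Check of the 50% assumption: not available.

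**4. What is recovered once the reference arm is defined**

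If all 20 reference patients are analysed, the true 6-month rate is near 50% and nobody is censored before 6 months, then SE = √(0.50 × 0.50 / 20) = 0.112, about 11 percentage points. At 54% the value is almost the same: √(0.54 × 0.46 / 20) = 0.111.

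**5. Sets after correction**

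- Fleming set: 6 phase I patients at the recommended dose (the stated minimum) + 34 = 40.
- Reference set: 20.
- Randomised patients only: about 34 versus 20, because the phase I patients were not randomised.

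**The case against.** The strongest reply is that the intent is plain. A specific instruction to estimate survival in both arms, a few lines below a general population sentence, shows that the injection criterion was meant for AGuIX patients. The article condenses a fuller protocol, the trial is declared non-comparative, and neither primary endpoint is touched. What is at stake is a descriptive estimate from 20 patients with a standard error of about 11 points, a loose check even after repair.

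Most of this stands, and it limits the harm. It does not remove the contradiction: the text does not restrict the criterion to AGuIX patients, and reading it that way still leaves the reference arm without an entry rule.

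Three stronger readings are tempting, and the article does not support them.

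- A reader might infer that the efficacy analysis would mix dose levels, because the population sentence has no dose condition. The Study design, objectives and Sample size sections already limit the phase II experimental arm to the recommended dose. Phase I patients injected at other doses belong in the injected population, because toxicity percentages are reported for every dose tested.
- A reader might infer that the phase II conclusion is compromised. The Fleming rule is applied to the experimental arm alone, and its figures do not change.
- A reader might infer that a valid randomised comparison is broken. No formal comparison is planned, and the experimental set includes by design at least 6 patients who were not randomised. The valid remainder is narrower: a side-by-side display should use like-for-like sets.

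**Conclusion.** The contradiction is real and is confined to the reference arm. As written, 0 of 20 reference patients qualify for analysis, so the promised reference-arm survival estimates and the check of the 50% assumption both fall away. The Fleming design (37 patients, at least 24 successes, exact alpha 0.0494, power 0.807) and the phase I dose finding are unaffected.

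The head count assumes the planned numbers and no AGuIX in the reference arm, as the treatment sections state. The 11-point standard error assumes 20 evaluable patients, no early censoring and a rate near 50%. The figure of 34 randomised experimental patients assumes that the plan's 34 additional patients are enrolled.

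**What to change.** Replace the population sentence with one short paragraph that does three things.

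1. Limit the injection criterion to AGuIX-treated patients: phase I, and the phase II experimental arm including the phase I patients treated at the recommended dose. The latter is the set for the Fleming analysis.
2. Define the reference-arm population as all patients randomised to that arm. Use it for the reference-arm Kaplan–Meier estimates and the check against 50%.
3. For any display that puts the arms side by side, show randomised patients as randomised, about 34 versus 20. Label it separately from the Fleming set of 40, which includes non-randomised phase I patients. This also avoids unmatched entry points: an injection filter starts 3 to 7 days before radio-chemotherapy, and a rule based on starting radiotherapy and temozolomide starts later.

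The cost is one paragraph of wording and one extra labelled display, with no added patients or data. It should be settled before outcomes are reviewed.

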### Study objectives and endpoints

#### Mains objectives and endpoints

The primary objectives of the NANO-GBM study are i) in the phase I part, to determine the recommended dose of AGuIX in combination with radiotherapy and TMZ during the concurrent radio-chemotherapy period for phase II (RP2D); ii) in the phase II part, to estimate the efficacy of the combination radio-chemotherapy + AGuIX (at the RP2D).

The first primary endpoint (phase I) is the RP2D of AGuIX nanoparticles corresponding to the highest dose tested for which the percentage of dose-limiting toxicities (DLT) is less than 33%. DLT is defined as any grade 3–4 toxicity according to the NCI-CTCAE classification v5.0, except for alopecia, nausea and vomiting, or fever, which can be managed by symptomatic treatment. Only toxicities occurring during the concomitant radio-chemotherapy (i.e. during 6 weeks) will be considered for DLT assessment.

The second primary endpoint (phase II) is 6-month progression-free survival rate (6-month PFS) to estimate the efficacy of the combination of radio-chemotherapy with AGuIX. Disease assessment throughout the study will be based on RANO (Response Assessment in Neuro-Oncology) criteria that take into account imaging progression (MRI) and also clinical status and level of steroid therapy [17].

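### The phase II primary endpoint is estimated by Kaplan-Meier but judged by a Fleming success count, and a cut-off is fixed only for 37 evaluable patients although 40 are enrolled

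*Protocol article*

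**What the plan says.** Mains objectives and endpoints: "The second primary endpoint (phase II) is 6-month progression-free survival rate (6-month PFS"), with disease assessed by RANO criteria.

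Sample size: the experimental arm follows a single-stage Fleming design "based on an acceptable success rate of 70% and a 50% unacceptable success rate", with one-sided alpha 5% and beta 20%. The minimum is 37 patients, and phase II is positive at 24 successes out of 37. The estimate at that cut-off is given as about 65%, "with a 90% confidence interval (90% CI) of 51.4%-76.7% (Jeffreys interval"). Forty patients are enrolled to absorb about 10% missing data.

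Data analysis: one sentence lists PFS, its 6- and 12-month rates, and ends "overall survival at 6 months and 12 months will be estimated by the Kaplan–Meier method in both arms". The next says of the primary endpoint: "6-month PFS in the experimental arm, will be calculated with its 90% CI, and the result will be interpreted according to the Fleming method". On incomplete data the section says only "Missing data will not be replaced".

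**The concern.** A Kaplan-Meier rate is not a number of successes. It uses patients lost before 6 months up to the time of censoring, and its usual interval (Greenwood variance) is not the Jeffreys interval. A Fleming count needs a yes or no for each patient and a fixed denominator. The article applies the second to a result obtained by the first and gives no link between them.

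The rule also exists for one denominator only. With 40 enrolled, 37 evaluable means a loss of 3/40 = 7.5%. The stated 10% loss leaves 36, and a smaller loss leaves 38 to 40. No cut-off is given for any of these. What is at stake is the 5% false-positive limit on the trial's efficacy conclusion, and whether the reported estimate and the decision agree.

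**Working it through.** **Inputs.** From Sample size: unacceptable rate p0 = 0.50, acceptable rate p1 = 0.70, one-sided alpha 0.05, power 0.80, rule 24/37, 40 enrolled, about 10% missing. From Data analysis: Kaplan-Meier estimator, 90% CI, Fleming interpretation. Numbers and times of losses in the examples are assumptions, set to the stated 10% (4 of 40).

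**1. The stated design reproduces.** With X binomial(37, p):
- alpha = P(X ≥ 24 | p = 0.50) = 0.0494
- power = P(X ≥ 24 | p = 0.70) = 0.807
- 37 is the smallest n meeting both limits (normal approximation 36.5)
- Jeffreys 90% CI, from the 5% and 95% points of Beta(24.5, 13.5): 51.4% to 76.6% (stated 76.7%, a trivial difference)

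With exactly 37 patients and no censoring before 6 months, Kaplan-Meier equals 24/37 = 64.9%, its log-log lower 90% limit is 50.4%, and the two methods agree.

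**2. With losses before 6 months they can part.** Take 40 patients: 5 progress at day 70, 4 are lost just after, 8 progress at day 154, and 23 are progression-free at 6 months.
- KM = (35/40) × (23/31) = 0.649
- Greenwood sum = 5/(40×35) + 8/(31×23) = 0.00357 + 0.01122 = 0.01479; standard error = 0.649 × √0.01479 = 0.079
- Lower 90% limits: plain 51.9%, log 53.1%, log-log 50.3%

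The estimate equals the 24/37 benchmark to one decimal and all three limits exceed 50%. The count is 23 of 36 evaluable. P(X ≥ 23 | 36, 0.50) = 0.066, above 0.05, so the exact cut-off at 36 is 24 (alpha 0.033) and the count is negative. The Jeffreys lower limit at 23/36 is 50.2%, so even the binomial interval can exclude 50% when the count fails.

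**3. The cut-off of 24 does not carry over to more than 37.** P(X ≥ 24 | n, 0.50):

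| Evaluable n | Alpha with cut-off 24 | Exact cut-off | Alpha | Power at 70% |
|---|---|---|---|---|
| 35 | – | 23 | 0.045 | 0.773 |
| 36 | 0.033 | 24 | 0.033 | 0.737 |
| 37 | 0.049 | 24 | 0.049 | 0.807 |
| 38 | 0.072 | 25 | 0.036 | 0.774 |
| 39 | 0.100 | 26 | 0.027 | 0.740 |
| 40 | 0.134 | 26 | 0.040 | 0.807 |

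For example, 24/40 with no losses meets a literal count of 24, yet Kaplan-Meier is 60.0% with a log-log 90% CI of 46.1% to 71.4%.

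**4. How often.** A simulation of 10,000 trials (40 patients, exponential PFS, independent censoring, 10% lost by 6 months) compared a count of at least 24 with a log-log Kaplan-Meier lower limit above 50%. They disagreed in 2.6% of trials at a true rate of 50%, 10.3% at 60% and 11.7% at 70%.

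**The case against.** The strongest reply is that there is only one decision rule. Data analysis says the result is interpreted by Fleming, and nothing makes a Kaplan-Meier limit above 50% a criterion of success. That stands. A reader might infer that the plan sets up two formal tests between which the sponsor could choose after seeing the data; the article does not support that. The contrast is between the one decision rule and the estimate reported beside it.

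A second reply is that rules for censored or non-evaluable patients belong in the analysis plan, which is not shown. That stands for the detail. It does not remove the mismatch, since the article itself names both the estimator and the count for the same endpoint, and fixes a cut-off for one denominator while enrolling another number.

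Third, the statement on missing data rules out replacement; it does not say that lost patients leave the denominator. That they do is an inference, though a natural one from enrolling 40 to secure 37.

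Fourth, a reader might fear that losses are mostly failures. Suppose 10% are lost and excluded, with cut-offs by evaluable number. Simulated alpha is then 3.8% if loss is random, about 6% if failures are twice as likely to be lost, and 13.4% if every lost patient is a failure. Those last two are assumed scenarios. The article gives no sign of such loss, and RANO's use of clinical status and steroid level lets some deteriorating patients be classed as progressed without relying on imaging alone. Informative loss would bias Kaplan-Meier too, so it is a separate matter from the mismatch.

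Finally, the example is borderline by construction, one success short, and in most simulated trials the two readings agree.

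**Conclusion.** The concern holds in a limited form. The sample size and the 24/37 rule are correct. What is badly fixed is the link between them and the analysis: the named estimator yields no success count, and the only cut-off belongs to 37 evaluable patients out of 40 enrolled.

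The firmest figure is the alpha of 0.072, 0.100 or 0.134 when 24 is applied to 38, 39 or 40 evaluable patients. It is exact and needs no assumption beyond that literal reading of the cut-off. The Kaplan-Meier contradiction (64.9% with a lower limit above 50%, against a negative 23/36) depends on assumed loss times but uses the plan's own 10%. The simulated disagreement of about 10% to 12% at true rates of 60% to 70% rests on independent exponential censoring. This should be corrected before analysis; it does not undermine the design.

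**What to change.** State in the protocol or analysis plan, before analysis:

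- The sole primary decision is the exact binomial count of patients progression-free at 6 months, reported with the Jeffreys 90% CI. The count decides, not the interval.
- Cut-offs by evaluable number: 23/35, 24/36, 24/37, 25/38, 26/39, 26/40.
- Kaplan-Meier estimates of PFS at 6 months are descriptive.
- How a patient with unknown 6-month status is counted. This should cover a patient clear at the week 23 MRI (day 154) and lost before the week 35 visit, since those are the scheduled disease MRIs on either side of 6 months.
- A sensitivity analysis counting every unknown status as failure.

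The PFS definition should stay as it is. Counting withdrawal for toxicity or a new treatment as failure would change the endpoint and is not needed here.

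The cost is a few sentences and one extra analysis. Power is a little below 80% at some evaluable numbers (about 0.74 to 0.77 at 35, 36, 38 and 39) and 0.807 at 37 and 40. The missing-as-failure analysis should remain a sensitivity analysis. With 26/40, a true rate of 70% and loss unrelated to outcome, the success probability per patient falls to 0.70 × 0.95 = 0.665 at 5% loss and 0.70 × 0.90 = 0.63 at 10%, so power drops to 0.65 and 0.47.
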